**Fig. 1 Fig1:**
[figure not shown]
Flow diagram of the study protocol

### Groups

#### Experimental group

Patients randomized into experimental group will benefit from TMR undertaken by a hospital-based team composed of a clinical pharmacist and a geriatrically-trained internal medicine specialist. For the purposes of issuing quality validation and relevant guidelines, TMR requires:
medication reconciliation to have an exhaustive list of all medications taken by the patient (including prescription and non-prescription medication);inclusion of the most recent results from laboratory tests (blood sodium, potassium and creatinine levels) and clinical data (blood pressure, weight);knowledge of patient history, active comorbidity and geriatric syndromes.

TMR means undertaking multidisciplinary medication reviews and taking into consideration all available sociodemographic, clinical, biological and pharmaceutical data pertaining to patients to optimize their therapeutic management.

It should be noted that an exhaustive list of patient medications will be acquired through medication reconciliation in accordance with the guidelines of French National Authority for Health [25].

Each drug prescription will be assessed in light of patient medical conditions, level of dependence and quality of life (amount, dosage, route of administration, contra-indications, drug interaction, and precautions for use). Medication databases will be consulted, following which adjustments to prescriptions can be made using the explicit criteria from STOPP/START.v2 criteria coupled with an implicit approach (the Medication Appropriateness Index) and taking into consideration existing therapeutic guidelines. A written report summarizing any proposed therapeutic adjustments will be produced and officialized as a personalized pharmaceutical plan (PPP) signed by both physician and pharmacist. The conclusions resulting from TMR will be transmitted to healthcare professionals within a maximum of 5 days after patients have been randomized to the experimental group. Should a therapeutic error with repercussions for patient prognosis be detected, the coordinating physician and patient’s GP will be informed immediately by phone. The GP can accept or reject the medication adjustments proposed by TMR. Data relevant to the study will be collected at the inclusion, 3 and 6 months.

#### Control group: standard care management

Control group patients will receive standard care from the medical and paramedical team of the nursing home where they reside. No medication reconciliation or medication review of their prescribed drugs will be conducted. Data relevant to the study will be collected at the inclusion, 3 and 6 months.

### Study aims

The objective of this study is to reduce unplanned hospital admission using TMR and determine which organizational and medico-psychosocial factors facilitating or hampering TMR development.

#### Primary endpoint

The primary endpoint is the rate of all-cause unplanned hospital admission occurring within 3 months of randomization. All-cause hospital admission is defined as a unplanned hospital stay in a medical or surgery department or intensive care unit, irrespective of reason for admission or duration of stay.

#### Secondary endpoints

Assessment of unplanned hospital admission at 6 months post-randomization will be complemented by the following endpoints:
Number of unplanned hospital admissions at 6 months post-randomization.Quality of life (QoL) of nursing home residents will be evaluated by the validated french version of EuroQol five-dimension three-level (EQ-5D-3 L) generic quality-of-life questionnaire [26, 27]. The questionnaire consists of two parts: the EQ-5D descriptive system and the EQ visual analogue scale (EQ VAS). The EQ-5D-3 L descriptive system comprises five dimensions as follows: mobility, self-care, usual activities, pain/discomfort and anxiety/depression. Each dimension has 3 levels: no problems, some problems, and extreme problems. The patient is asked to indicate his/her health state by ticking the box next to the most appropriate statement for each of the five dimensions. Each response generates a 1-digit number that represents the level selected for that dimension. The EQ VAS records self-rated patient health on a vertical visual analogue scale where the endpoints are labelled ‘best imaginable health state’ and ‘worst imaginable health state’. The EQ-5D-3 L questionnaire will be administered at the inclusion, at 3- and 6-month follow-up.Incidence of behavioral disturbances will be assessed by the validated french version of Neuropsychiatric Inventory (NPI) questionnaire at the inclusion, at 3- and 6-month follow-up [28]. NPI scoring is based on interviews with main caregivers. The NPI assesses the frequency (4-point scale) and severity (3-point scale) of 10 neuropsychiatric disturbances (delusions, hallucinations, agitation, dysphoria, anxiety, euphoria, apathy, disinhibition, irritability, and aberrant motor behavior), and a score from 0 to 12 is obtained for each scale by multiplying frequency by severity. The total NPI score is the sum of the subscale scores.The number of falls at 3- and 6-months post-randomization.The proportion of residents who will have been subjected to at least 1 potentially inappropriate prescription at the inclusion, 3 and 6 months. STOPP and START tool will be used for explicit criteria (French version 2). The implicit approach includes all available medical data, potential self-medication, and questions from the Medication Appropriateness Index [29].Nursing staff satisfaction with methods of medication administration to residents, number of oral medications dispensed, choice of galenic formulation, time spent on drug administration, and treatment dispensed to a patient consistent with that patient’s state of health. Satisfaction will be evaluated using 5-point Likert scales at the inclusion and at 3 months.Description of therapeutic recommendations which will have been proposed and GP’ adherence rate of its at 3- and 6-months.Characteristics of patients whose GP have taken account of TMR recommendations.Cost-effectiveness ratio of TMR versus standard care at 6-month follow-up (see details in Health Economic Analysis section below).The present study will also attempt to determine which organizational and psychosocial factors are likely to facilitate or on the contrary to hamper TMR development and acceptability (see details in Evaluation of Acceptability/Satisfaction section below).

### Study procedures

The evaluation will be performed at three different time points: baseline, 3 and 6 months after the randomization (Table 1). Data collection will be conducted by a clinical research assistant and reported in the Case Report Form.

The source of this data will be resident medical records and visits to residents and their care providers to complete the questionnaires. Participant’s file and electronic data are store security of the study site. Patient data are only identifiable with the unique participant’s hospital registration number. This variable will be deleted once the data is completed making the dataset anonymous. This process is in accordance to MR-001 methodology.

All adverse events will be declared to the promotor within 24 h. Causal relationship between adverse events and TMR will be analyzed.

### Data management and analysis

Data will be monitored by a clinical research monitor. Inconsistencies will be reported to the study investigators in order to decide whether the data should be corrected or considered as missing data. Statistical analysis will be performed after checking the database. After freezing, the consolidated data will be processed by statistician. The modified intention-to-treat population (including all randomized subjects evaluated at least at baseline; patients having withdrawn consent will be excluded from the final analysis) will be used in the primary analysis. No interim analysis is planned. Baseline parameters will be presented by group (control and experimental). No comparisons will be made in accordance with CONSORT guidelines.

#### Primary endpoint

All-cause unplanned hospital admission rates (see Primary Endpoint above) will be compared between the 2 groups (control vs experimental) using Chi-square or Fisher’s exact tests (as primary analysis). The results will be summarized as relative risks and its 95 95% CI.

As secondary analysis: i) survival estimates will be calculated in line with the Kaplan–Meier method and compared using a log-rank test; ii) adjusted analysis will be applied to potential confounding factors (difference observed in baseline characteristics) using logistic regression. A potential center effect will be assessed by mixed-effects modeling using generalized linear mixed model methodology (SAS software, 9.4 version, GLIMMIX procedure, center as a random effect). The result will be summarized in terms of odd ratios and associated 95% CI; iii) heterogeneity of the effect among pre-specified subgroups will be tested using the hazard ratio test and 95% CI, provided per subgroup.

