### Recruitment and randomization

Recruitment will take place within consenting nursing homes contacted by the gerontology coordination groups of Marseille. Nursing home coordinating physicians will act as study investigators in charge of patient inclusion. Written consent to participate will be obtained at the Nursing home after the investigator has provided all necessary information about the study. Randomization will be performed at patient level, with eligible patients randomly assigned in a 1:1 ratio to the control group (non-intervention) or the experimental group (TMR) based on a computer-generated permuted-block randomization schedule with blocks of four. Randomization is to be stratified by an adverse drug event risk detection score in elderly patients, the Trivalle’s risk score (≤ 5 or > 5). Based on the IMEPAG study [21], this score is both easy and practical to use for detecting the risk of adverse drug events in elderly patients. Risk factors included in the score are: number of medications (if greater than or equal to 7), antipsychotic treatment and recent anticoagulant treatment (dating back less than 3 months). Each parameter is scored on a scale from 0 to 10, with 0–1 corresponding to an adverse drug event risk of 12%, 2–5 corresponding to a 32% risk and 6–10 to a 53% risk.

Computer-generated randomized lists will be drawn up before the beginning of the study under the responsibility of the local Clinical Research Unit. Methodological support will be provided by the Clinical Research Unit. Study investigators will not be blinded to group allocation. The recruitment period will span 20 months, and patient follow-up will last 6 months (Table 1).

**Table 1 Tab1:** Timeline of the study

Timepoint	Study Period			
	Enrolment	Inital assessment	Follow-up at 3 months	Follow-up at 6 months

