### Sample size

On the basis of a unplanned hospital admission rate of 25% over a 3-month period [23] and taking into consideration the results of a study evaluating the impact at 8 weeks of medication review on admission to nursing home [24], we estimate a unplanned hospital admission rate of 10% in the experimental group. The initial sample size of 292 patients provided 90% power to detect this difference at a two tailed significance level of 0.05. Assuming possibly 25% of patients lost to follow-up, a total of 364 patients is required (182 per group) (Fig. 1).

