
In the present study, we have attempted to keep the exclusion criteria for patients enrolled in the study to a minimum. Thus, patients under limited or general guardianship who are usually excluded from trials can perfectly well be included with the agreement of their legal representative. Likewise, we wished to include patients at both high and low risk of iatrogenic disease yet equally wished to be able to evaluate the impact of the intervention in terms of Trivalle’s score, which explains why randomization is stratified by the Trivalle’s risk score. On the other hand, for the purposes of investigating resident quality of life we decided to exclude patients with an MMSE score of less than 18. Changes to medication are equally more difficult to implement in patients suffering from severe cognitive impairment for fear of exacerbating their condition [51]. The long-term goal, should the benefits of medication review be proven, is to extend its use to all nursing home residents as part of telemedicine services.

By way of conclusion, the results from this randomized trial are expected to confirm that medication review via TE could be a worthwhile care management strategy for nursing home residents.

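### Randomization is stratified by Trivalle score, but the primary test leaves the stratum out (at small cost) and the heterogeneity analysis states no comparison between strata

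*Protocol article*

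**What the plan says.** **Design.** Under Recruitment and randomization: "Randomization is to be stratified by an adverse drug event risk detection score in elderly patients", the Trivalle score, cut at 5. Eligible scores run from 2 to 10. The same section gives adverse drug event risks of 32% for scores 2–5 and 53% for scores 6–10. The Discussion explains that the authors "wished to be able to evaluate the impact of the intervention in terms of" this score, and gives that as the reason for stratifying.

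**Primary analysis.** Under Data management and analysis, Primary endpoint, admission rates "will be compared between the 2 groups (control vs experimental) using Chi-square" or Fisher's exact tests, summarized as a relative risk with 95% CI. No stratum term is mentioned.

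**Secondary analyses of the same endpoint.** The log-rank test is not described as stratified. The logistic model adjusts for factors showing a difference at baseline. The mixed model adds center only.

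**Heterogeneity.** "heterogeneity of the effect among pre-specified subgroups will be tested using the hazard ratio test and 95% CI, provided per subgroup". The article does not name the subgroups, an interaction term or a hazard model.

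**The concern.** Stratified allocation forces the two arms to have nearly the same mix of risk strata. A crude test still counts the between-stratum variation as noise, so if the stratum predicts admission the standard error is too large, the test rejects less often than its nominal level, and some power is given away. The adjusted analysis does not repair this: a rule that picks covariates because they differ at baseline will tend to omit the one factor that the design keeps from differing.

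On heterogeneity, a hazard ratio with its interval in each subgroup shows whether the effect differs from 1 there. It does not show whether the effects differ from each other. At stake is the question that the Discussion gives as the reason for stratifying. If the results were read subgroup by subgroup, chance alone could look like a different effect by risk stratum.

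**Working it through.** **1. Reproduce the planned size.** Inputs from Sample size: "On the basis of a unplanned hospital admission rate of 25% over a 3-month period"; "we estimate a unplanned hospital admission rate of 10% in the experimental group"; 90% power; "at a two tailed significance level of 0.05".

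Two-proportion formula with mean rate 0.175 and difference 0.15:

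n = [1.960·√(2·0.175·0.825) + 1.282·√(0.25·0.75 + 0.10·0.90)]² / 0.15² = 132.8 per arm

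Continuity correction: n' = (n/4)·[1 + √(1 + 4/(n·0.15))]² = 145.8, so 146 per arm and 292 in total. This matches "The initial sample size of 292 patients provided 90% power to detect this difference". The planned relative risk is 0.10/0.25 = 0.40.

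**2. What is not in the documents.** They give neither the share of patients per stratum nor admission rates by stratum. Assumed here: 60% in the lower stratum and an overall control rate of 25%. The only documented gradient is 53/32 = 1.66, and it concerns adverse drug events, so it is a proxy for admission risk.

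**3. Size of the crude test, analytically.** Under the null the crude variance uses 0.25·0.75 = 0.1875. The true variance under balance within strata is 0.1875 − 0.6·0.4·(p₂ − p₁)². Actual type I error = 2·[1 − Φ(1.960/√ratio)], where ratio is true over crude variance.

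| Control rates | Risk ratio | Between-stratum part | Variance ratio | Type I error |
|---|---|---|---|---|
| 20% / 32.5% | 1.63 | 0.00375 | 0.980 | 4.8% |
| 18% / 35.5% | 1.97 | 0.00735 | 0.961 | 4.6% |
| 15% / 40% | 2.67 | 0.01500 | 0.920 | 4.1% |

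**4. Simulation.** 400,000 trials per cell, 146 per arm, balance within stratum, uncorrected chi-square against CMH:

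| Control rates | Type I error, crude / CMH | Power at RR 0.40, crude / CMH | Power at RR 0.55, crude / CMH |
|---|---|---|---|
| 20% / 32.5% | 4.8% / 5.0% | 93.4% / 93.4% | 68.9% / 69.3% |
| 18% / 35.5% | 4.6% / 5.0% | 93.5% / 93.7% | 68.9% / 69.8% |
| 15% / 40% | 4.1% / 5.0% | 93.7% / 94.2% | 69.3% / 71.3% |

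The gain from stratifying is therefore about 0 to 0.5 points at the design effect and 0.4 to 2.0 points at a relative risk of 0.55.

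**5. Wider assumptions.** With 30–70% of patients in the lower stratum and a risk ratio of 1.66, crude type I error is 4.7–4.9% and power is 93.2–93.5% for both tests. At ratios of 2.5 to 4, crude type I error falls to 3.1–4.7%, CMH stays at 4.9–5.1%, and the CMH gain at a relative risk of 0.40 is about 0.2–1.1 points.

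**6. Power of an interaction test.** Assume two equal strata with a risk ratio of 1.66 and an overall control rate of 25%: control rates 18.8% and 31.2%, experimental rates 0.40 times these. With m per arm per stratum, the variance of the log ratio of relative risks is the sum of (1 − p)/(m·p) over the four cells.

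- m = 73 (146 per arm): 0.0591 + 0.0302 + 0.1682 + 0.0961 = 0.354, SE 0.595. Ratio detectable with 80% power: exp(2.802·0.595) = 5.3.
- m = 91 (182 per arm): 0.0474 + 0.0243 + 0.1350 + 0.0771 = 0.284, SE 0.533. Ratio detectable: exp(2.802·0.533) = 4.4.

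**7. What separate subgroup tests would show under a constant effect.** In the same setting with 146 per arm, simulated power is 0.534 in the lower stratum and 0.796 in the upper. The chance that exactly one is significant is 0.534·0.204 + 0.796·0.466 = 0.48. With 182 per arm it is 0.40.

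**The case against.** **The primary-test half has little consequence.** This stands. At the documented gradient the power of the two tests is practically the same, and the larger figures above need a steeper gradient or a smaller effect than the plan assumes. The true gradient may also be weaker than 1.66, because the endpoint is admission for any cause and the Background attributes only a minority of older adults' admissions to medication. At an assumed ratio of 1.16 the two tests cannot be told apart (type I error 5.04% crude, 5.00% CMH). The crude relative risk is a legitimate marginal estimate. A reader might infer that ignoring the stratum makes the primary result invalid or inflates false positives. The calculation shows the opposite direction: slight conservatism.

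**The heterogeneity wording may only be loose.** This stands in part. The phrase could be shorthand for an interaction test in a Cox model, and time-to-event methods are planned for this endpoint. Naming the hazard model and listing the subgroups are details that an article commonly leaves to the full protocol or SAP. A reader might infer that the plan will compare subgroup p-values and so answer the subgroup question invalidly. The article states no such rule, so the 40–48% discordance describes a misreading that the wording permits, not a planned procedure. What remains is that the one sentence on heterogeneity names a test that is not a recognized test of heterogeneity and states no comparison between subgroups.

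**Conclusion.** The point holds at modest size. The article itself fixes an unstratified primary test after stratified randomization and a covariate rule that would normally miss the stratum. This is therefore a stated choice, not a detail left to the SAP. The test is valid and slightly conservative: about 4.8% instead of 5.0% near the documented risk ratio, and about 4.1% at a ratio of 2.7. The sample size is unaffected, and the power at issue is about half a point or less at the planned effect and up to about 2 points at a relative risk of 0.55. These figures rest on the assumed 60/40 split and on adverse-drug-event risk standing in for admission risk.

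The heterogeneity wording matters more, because effect by Trivalle score is a declared purpose of the design and the stated method does not clearly address it. The finding is ambiguity, not demonstrated invalidity. Even a correct interaction test would detect only very large differences between strata.

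**What to change.** 1. Make the primary analysis a CMH test stratified by Trivalle stratum (≤ 5, > 5), with the Mantel-Haenszel relative risk and 95% CI. Keep the crude chi-square or Fisher test as a sensitivity analysis.
2. Put the stratum in the logistic model as a fixed covariate whether or not a baseline difference is seen, and stratify the log-rank test by it.
3. Replace the hazard-ratio sentence with a treatment-by-Trivalle-stratum interaction test, preferably on the relative risk scale of the primary analysis. Give subgroup estimates and 95% CIs as description only.
4. State that the interaction test reaches 80% power only for a ratio of relative risks of about 4.4 (182 per arm) to 5.3 (146 per arm), under the assumptions of step 6 of the working, so that a non-significant result is not read as evidence of equal effects.

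The cost is wording in the analysis section and SAP, to be settled before unblinded analysis. The score is recorded at enrolment for every randomized patient, so neither data collection nor sample size changes.

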### Exclusion criteria

Patients who exhibit any of the following criteria will be excluded: life expectancy < 3 months; involvement in another research project; medication review conducted by a pharmacist in the last 6 months; mini mental state examination (MMSE) score < 18 [22].

Refusal to participate on the part of general practitioner (GP) constitutes a secondary exclusion criterion in this study.

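### Kaplan–Meier curves for unplanned admission leave out death as a competing event, and no comparison of deaths by arm is planned; the numerical effect is modest

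*Protocol article*

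**What the plan says.** The Primary endpoint section under Study aims reads: "The primary endpoint is the rate of all-cause unplanned hospital admission occurring within 3 months of randomization". Death is not a component. Mortality is also absent from the endpoint lists in the abstract, in Table 1 and in the Secondary endpoints section.

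Data management and analysis defines a modified intention-to-treat population. It leaves out only residents with no baseline evaluation and those who withdraw consent. The primary comparison is a chi-square or Fisher test with a relative risk. As a secondary analysis of the same endpoint, "survival estimates will be calculated in line with the Kaplan–Meier method and compared using a log-rank test". Hazard ratios by subgroup follow. Nothing is said about how a death enters either analysis.

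Eligibility excludes residents with "life expectancy < 3 months", and follow-up runs to 6 months. The planning rates are in Sample size: "On the basis of a unplanned hospital admission rate of 25% over a 3-month period", and for the other arm "we estimate a unplanned hospital admission rate of 10% in the experimental group".

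**The concern.** A resident who dies in the nursing home can no longer be admitted, so death competes with the event of interest. This touches the plan in two places.

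- **The curves.** Death is not part of the event, so a Kaplan–Meier curve for admission has to censor it. One minus that curve estimates admission risk in a hypothetical population where nobody dies, not the proportion of residents admitted.
- **The primary proportion.** Under the stated population, a resident who dies unadmitted stays in the denominator with no admission recorded, exactly like a resident who stays well.

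Mortality belongs to the trial's own rationale: the abstract names it among the harms of inappropriate prescribing, and the Discussion lists it among outcomes studied in earlier medication reviews. The intervention leads to changes in drugs. A fall in admissions is easier to interpret if deaths are compared beside it, and no such comparison is planned.

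**Working it through.** **Plan's own figure.** Inputs: 25% and 10%, "at a two tailed significance level of 0.05", 90% power, 1:1 allocation. The usual two-proportion formula gives 132.8, so 133 per arm. With continuity correction, 132.8/4 × (1 + √(1 + 4/(132.8 × 0.15)))² = 145.8, so 146 per arm and 292 in total. This matches "The initial sample size of 292 patients provided 90% power to detect this difference". The planned relative risk is 0.10/0.25 = 0.40.

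**Assumptions below.** Every mortality value is assumed. Hazards are constant over 3 months (time unit = 3 months), with λ for admission and μ for death.

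- Cumulative incidence of admission: CIF = λ/(λ+μ) × (1 − exp(−(λ+μ)))
- One minus Kaplan–Meier with deaths censored: 1 − exp(−λ)

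**A. Admission hazard set to give 25% if nobody died.** λ = −ln 0.75 = 0.2877 and μ = −ln(1 − d).

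- d = 5%: μ = 0.0513; CIF = (0.2877/0.3390) × (1 − 0.7125) = 24.4%, against 25.0%.
- d = 10%: μ = 0.1054; CIF = (0.2877/0.3930) × (1 − 0.6750) = 23.8%, against 25.0%.

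The excess is 0.6 to 1.2 points.

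**B. True proportions admitted fixed at the planned 25% and 10%.** Let q be the risk of death before admission, equal in both arms, and p the risk of admission. Then λ = −ln(1 − p − q) × p/(p + q).

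| q (assumed) | 1−KM, control | 1−KM, experimental | Ratio |
|---|---|---|---|
| 1% | 25.1% | 10.05% | 0.400 |
| 3% | 25.4% | 10.2% | 0.400 |
| 5% | 25.7% | 10.3% | 0.399 |
| 10% | 26.5% | 10.6% | 0.399 |

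The largest excess is about 1.5 points, and the ratio hardly moves from 0.40.

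**C. No effect on admission (λ = 0.2877 in both arms), unequal deaths, unadmitted deaths counted as non-events.**

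| Deaths, control vs experimental (assumed) | CIF, control vs experimental | Spurious relative risk |
|---|---|---|
| 3% vs 6% | 24.64% vs 24.28% | 0.985 |
| 5% vs 10% | 24.40% vs 23.79% | 0.975 |
| 5% vs 15% | 24.40% vs 23.16% | 0.949 |

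**D. Admission-or-death as a supportive comparison.** Rates are 25% + q and 10% + q, with 146 per arm and no continuity correction. Power is 92.5% at q = 0, 89.2% at 3%, 87.0% at 5% and 82.2% at 10%.

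**The case against.** The strongest reply is that the article never says how deaths are coded. They might be non-events, might fall within the 25% allowance for loss to follow-up, or might be covered by a rule in the full protocol or analysis plan, neither of which is shown. That stands: a missing coding rule is not the point here. The point rests on what the article does fix, namely an endpoint list without death and a named estimator that does not allow for it.

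Three stronger readings are tempting but not supported.

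- A reader might infer that the primary result is biased because deaths count as successes. The coding is an inference from the population definition, and the comparison favours an arm only if mortality differs between arms. Larger distortions need inputs the document does not contain: 4 points more deaths among residents with a 60% chance of admission would remove 0.04 × 0.60 = 2.4 points, against a planned 15.
- A reader might extend the overstatement to 6 months, where it would be larger. The Kaplan–Meier analysis sits under the 3-month primary endpoint, and 6-month proportions fall under chi-square or Fisher tests, so a 6-month curve is not clearly planned.
- A reader might say that nothing would reveal excess deaths. Study procedures requires adverse events to be declared and their relation to the review analysed, and the QALYs in the Health economic analysis depend on survival time. Neither is a planned comparison of deaths by arm, but they are not nothing.

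The log-rank test is also not at fault. With deaths censored it validly compares cause-specific admission hazards. The screen on life expectancy further limits early deaths.

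**Conclusion.** The concern holds in a limited form. Kaplan–Meier is the wrong estimator for the probability of a non-fatal admission when residents can die first, and the plan contains no comparison showing whether fewer admissions come with more deaths. The overstatement of the curve at 3 months is about 0.6 to 1.5 points for assumed mortality of 5% to 10%. It affects a secondary analysis and nearly cancels in the ratio between arms. Unequal mortality alone gave relative risks of 0.95 to 0.985, far from the planned 0.40. These sizes rest on constant hazards, on assumed mortality, and on residents who die having the same admission hazard as the rest; a dependence between the two would change them. The primary test and the sample size need not change. The revision is still worthwhile because it is cheap and makes the result interpretable.

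**What to change.** 1. Keep the chi-square or Fisher test as primary, and state that residents who die remain in the denominator.
2. Report deaths by arm at 3 and 6 months.
3. Add unplanned admission or death within 3 months as a supportive comparison, using the same test as the primary.
4. Replace the one-minus-Kaplan–Meier curves by Aalen–Johansen cumulative incidence of admission, with death as a competing event.
5. Keep the log-rank test, labelled as a comparison of cause-specific hazards, and give cause-specific hazard ratios for both admission and death. Do not replace it by Gray's test: that test compares cumulative incidence, which falls when deaths rise, so it would credit the arm with more deaths.

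The cost is some wording and a few lines of code. Resident medical records are already the data source, and the QALYs already need survival time. The composite is less specific to drug harm and has somewhat lower power (about 89% to 82% at 146 per arm with 3% to 10% deaths), so it should stay supportive.

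### The secondary adjusted analysis takes its covariates from chance baseline differences rather than a fixed prognostic list, and its odds ratio is not directly comparable with the primary relative risk

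*Protocol article*

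**What the plan says.** All places are in the Methods of the protocol article.

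- **Data management and analysis.** Baseline data are tabulated by arm, and the next sentence is "No comparisons will be made in accordance with CONSORT guidelines".
- **Data management and analysis, Primary endpoint, primary analysis.** An unadjusted chi-square or Fisher test. "The results will be summarized as relative risks and its 95 95% CI".
- **Same section, secondary analysis ii.** "adjusted analysis will be applied to potential confounding factors (difference observed in baseline characteristics) using logistic regression". No covariate is named. A generalized linear mixed model with center as a random effect follows, and then "The result will be summarized in terms of odd ratios and associated 95% CI".
- **Recruitment and randomization.** Allocation is 1:1 at patient level in blocks of four. "Randomization is to be stratified by an adverse drug event risk detection score in elderly patients", namely the Trivalle score, cut at 5. The paragraph on the adjusted analysis does not mention this stratum.

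**The concern.** The bracket in secondary analysis ii is a selection rule, and it selects on the wrong property. In a randomized comparison, adjustment is worthwhile when a covariate predicts the outcome. Whether the arms happen to differ on it says nothing about that. A rule based on observed differences has three consequences:

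- The model is not known until the allocation-coded baseline table has been seen, and someone must then decide what counts as a difference.
- Variables with no bearing on admission can enter.
- Prognostic variables that happen to be balanced tend to be left out, and the precision they would bring is lost.

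The change of effect measure adds a problem of reading. A crude relative risk will stand next to an adjusted odds ratio, and a reader will be inclined to put the gap between them down to adjustment. Part of that gap is only the change of scale.

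**Working it through.** **1. Planning rates.** The Sample size section gives 25% (control) and 10% (experimental), 90% power, two-sided 0.05 and 292 patients before allowance for loss. To confirm that these rates drive the design:

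- Uncorrected: n = [1.960 × √(2 × 0.175 × 0.825) + 1.282 × √(0.25 × 0.75 + 0.10 × 0.90)]² / 0.15² = 132.8, so 133 per arm.
- Continuity-corrected: (132.8/4) × [1 + √(1 + 4/(132.8 × 0.15))]² = 145.8, so 146 per arm and 292 in all. The stated figure reproduces exactly.

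**2. Relative risk and odds ratio from the same data.**

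- RR = 0.10/0.25 = 0.40.
- OR = (0.10/0.90)/(0.25/0.75) = 0.1111/0.3333 = 0.33.
- With 182 per arm the expected events are 18.2 and 45.5.
- SE(log RR) = √(1/18.2 − 1/182 + 1/45.5 − 1/182) = 0.257, giving a 95% CI of 0.24 to 0.66.
- SE(log OR) = √(1/18.2 + 1/163.8 + 1/45.5 + 1/136.5) = 0.301, giving a 95% CI of 0.18 to 0.60.
- With RR held at 0.40, the OR is 0.375 at a control rate of 10% and 0.318 at 30%.

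The same result therefore reads as a 60% reduction in risk or a 67% reduction in odds. The odds ratio is also non-collapsible: conditioning on a prognostic covariate or a center effect moves it away from 1 even when the arms are perfectly balanced. A move from crude RR to adjusted OR thus mixes change of scale, non-collapsibility and adjustment.

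**3. How often chance alone would supply a covariate.** The protocol gives no threshold and no number of variables. Assuming a 5% screen on k independent variables, P(at least one) = 1 − 0.95^k:

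| k | P(at least one) |
|---|---|
| 5 | 23% |
| 10 | 40% |
| 15 | 54% |
| 20 | 64% |

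These figures are illustrative only. Table 1 lists about 11 patient-level items at enrolment or initial assessment, but they are not independent.

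**4. Type I error.** Null simulation: 4,000 trials of 364 patients, ten independent covariates of which three are prognostic (all assumed).

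| Analysis | 5% screen | 20% screen |
|---|---|---|
| Unadjusted | 4.7% | 4.7% |
| Fixed prognostic covariates | 4.5% | 5.0% |
| Covariates selected on imbalance | 4.2% | 4.0% |

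Selection on imbalance did not inflate the error and was slightly conservative.

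**5. The covariate most likely to be missed.** Inclusion requires a Trivalle score of 2 to 10. The Recruitment section attaches adverse drug event risks of 32% (scores 2–5) and 53% (scores 6–10) to the two bands that form the strata. Those are not admission rates, but this is the protocol's own risk marker. Stratified blocks of four should keep it nearly balanced, so a rule that looks for differences will tend to pass over it.

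**The case against.** **The two statements on baseline may not conflict.** The ban on comparisons directly follows the plan to tabulate by arm, and its natural reading is a table without p-values. Noticing a difference in that table is then allowed. This stands: a reader might infer a flat contradiction, but the text supports only a tension. The softer reading does leave the differences to be judged by eye, with no threshold.

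**No inferential harm is shown.** This stands for type I error. The rule uses baseline data and not outcomes, no interim analysis is planned, and the data are processed after the freeze. A reader might infer a biased or anti-conservative test; neither the documents nor the simulation supports that. The loss of precision follows from the reasoning but has not been quantified.

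**The 40% and 54% figures are not properties of this trial.** This stands. They need a significance screen that the protocol does not describe and that its ban on comparisons probably excludes.

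**Odds ratios are what these models give, and the scale is labelled.** This is fair. The sentence on odds ratios follows the one on the center effect and may describe the mixed model alone, although logistic regression gives an odds ratio by default. It would be too strong to say that the two measures cannot be set side by side, because an adjusted relative risk can be derived from the same model. The 0.40 against 0.33 gap is also small beside the interval for either.

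**The unseen analysis plan may list covariates.** It may. But the article does not leave the choice open: it states a rule. A plan that follows the rule inherits the fault, and a plan that does not departs from the published protocol.

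**Conclusion.** The point holds in a limited form. The stated rule makes one secondary analysis data-dependent, with an undefined threshold. It can admit non-prognostic variables, and it tends to drop balanced prognostic ones, the Trivalle stratum first among them. The odds ratio from that analysis is not directly comparable with the primary relative risk: 0.33 against 0.40 at the planning rates, and 0.375 to 0.318 for the same relative risk as the control rate runs from 10% to 30%. The odds ratio looks the stronger of the two only if there is an effect.

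The primary unadjusted test and the sample size are untouched. A reader might also infer a firm ceiling on the number of covariates from the expected events: 0.35 × 136.5 = 47.8 with 25% loss, or 0.35 × 182 = 63.7 with none. The documents contain no events-per-variable rule, so these counts argue for a short list but set no limit.

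The change should be made because it is better and nearly free. Leaving it would not invalidate the trial.

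**What to change.** Before unblinding, replace the bracket with a short covariate list that is used whatever balance is observed:

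- the Trivalle stratum (≤ 5 or > 5);
- a few prognostic variables recorded before randomization or ascertained identically in both arms, for example age (recorded at enrolment in Table 1) and a comorbidity measure defined as a count, an index or named conditions, with its source stated;
- center as the random effect already planned.

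Do not add a medication count. Seven or more medications is already a component of the Trivalle score. The Groups section also provides for medication reconciliation in the experimental arm only, so a count drawn from it would be ascertained differently by arm.

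Report an adjusted relative risk and risk difference by marginal standardization of the model, next to the odds ratio. State whether predictions are averaged over the center effect or conditional on it. Add a clause that the ban on baseline comparisons refers to significance tests, if that is what is meant.

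The cost is a few lines in the analysis plan and a short standardization step in the program. No new data and no change to the sample size are needed.
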